**Methods:**

This is a randomized, double-blind, single-center clinical study. We randomly assigned 690 participants to groups each administered 3 L of polyethylene glycol (PEG), 30 mL of hemp seed oil and 2 L of PEG, or 30 mL of hempseed oil, 2 L of PEG, and 1000 mL of 5% sugar brine. The Boston Bowel Preparation Scale was considered the primary outcome measure. We evaluated the interval between consumption of bowel preparation and first bowel movement. Secondary indicators included the time of cecal intubation, detection rate of polyps and adenomas, willingness to repeat the same bowel preparation, whether the protocol was tolerated, and whether there were adverse reactions during bowel preparation and were evaluated after counting the total number of bowel movements.

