### Trial design and setting

This is a double-blind, single-center, three-arm, non-inferiority study that will be conducted at the Surgical Endoscopy Center of the First Hospital of Lanzhou University from April 2022 to February 2023. Recruited participants will be randomly assigned to receive a combination of 3 L of PEG, 30 mL of hemp seed oil and 2 L of PEG, or 30 mL of hemp seed oil, 2 L of PEG, and 1000 mL of 5% sugar brine (Fig. 1).

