### Recruitment, randomization, and blinding

Investigators trained for the study and authorized by the principal investigator will assess the candidates according to the inclusion and exclusion criteria on the day before the colonoscopy. After eligible participants are identified, written informed consent will be obtained from each eligible patient, next of kin, or legal representative. On the consent form, participants will be asked whether they agree to the use of their data and biological specimens. Participants will be asked to agree to the research team sharing relevant data with regulatory authorities as appropriate. Researchers should collect clinical data, including gender, age, weight, BMI, history of the previous colonoscopy, history of abdominal surgery, cardiovascular and neurological diseases, and long-term use of certain drugs.

Initially, the SPSS version 22.0 software will be used to generate random sequences, and these will be subsequently put in an opaque envelope. The independent statistical expert used a computer to generate random numbers, and the participants were assigned to the following 3 groups in a 1:1:1 ratio, numbered sequentially after random assignment: A, 3L PEG; B, 30 mL of hempseed oil and 2 L of PEG; and C, 30 mL of hemp seed oil, 2 L of PEG, and 5% sugar brine. Moreover, researchers, endoscopic physicians, and participants will all be blinded during the examination to eliminate bias as much as possible.

At the end of the study, unblinding will be carried out by the principal investigator. The first unblinding will be conducted to uncover the groups of participants, followed by statistical analysis to clarify the differences between the groups, and a second unblinding will be conducted to further clarify the specific groups. When an emergency, such as a serious adverse event, threatens the safety of a subject and the subject’s grouping must be known, an emergency unblinding would be conducted. The unblinding of the specific time, reason, and name of the executive of the emergency will be timely recorded.

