### Study protocol

All subjects undergoing colonoscopy should start a no-pigment, low-residue, low-fiber diet 3 days before examination and fast at 18:00 the night before the examination. If hypoglycemia or other discomforts occur due to hunger on the same day, oral colorless vitamin drinks or candy bars can be taken to enhance tolerance. Moreover, to allay the participants’ fear of intestinal preparation, researchers should explain the purpose of colonoscopy, importance of adequate intestinal preparation, and potential adverse events that may occur during intestinal preparation.

Figure 2 depicts the drug use schemes of the 3 groups. The oral intestinal preparation process under the guidance of researchers in the 3 L of PEG group was as follows: one bag of PEG and 1 L of clear fluids was taken orally at 22:00 the day before the examination, the second bag was taken 4–6 h before the examination, and the third bag of PEG was taken half an hour later (Fig. 2A). As for the 30 mL of hemp seed oil and 2 L of the PEG group, patients orally took 15 mL of hemp seed oil in divided doses at 20:00 and 22:00 1 day before the examination, the first bag of PEG and 1 L of clear fluids 4–6 h before the examination, and the second bag of PEG half an hour later (Fig. 2B). Regarding the 30 mL of hemp seed oil, 2 L of PEG, and 5% sugar brine group, patients orally took 15 mL of hemp seed oil in divided doses at 20:00 and 22:00 1 day before the examination, the first bag of PEG and 1000 mL of 5% sugar brine 4–6 h before the examination, and another bag of PEG half an hour later (Fig. 2C). In the study, participants were free to drink clear fluids after the commencement of bowel preparation. The study schedule is shown in Fig. 3.

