#### Secondary outcomes

Adverse reactions that occur during bowel preparation are the secondary outcome indicators of the study. We evaluated the interval between taking bowel preparation and the first bowel movement, the total number of bowel movements completed, time of cecal intubation, detection rate of polyps and adenomas, willingness to repeat the same bowel preparation, whether the protocol is tolerated (0 points for no discomfort; 1 point for mild discomfort; 2 points for ability to tolerate; 3 points for not being able to tolerate), and adverse events.

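### The trial is called double-blind, but the written regimens reveal arm A versus arms B and C to participants and to staff guiding intake, so patient-reported outcomes in those comparisons are effectively open-label

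*Protocol article*

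**What the plan says.** The Abstract (Methods) states: "This is a randomized, double-blind, single-center clinical study". Trial design and setting repeats the label: "This is a double-blind, single-center, three-arm, non-inferiority study". The Discussion uses it again. Recruitment, randomization, and blinding says that "researchers, endoscopic physicians, and participants will all be blinded during the examination to eliminate bias as much as possible". The same section provides for emergency unblinding and for a two-stage unblinding at the end, with the statistical analysis placed between the stages.

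The Study protocol section describes what each arm takes:

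- **Arm A (3 L PEG).** "one bag of PEG and 1 L of clear fluids was taken orally at 22:00 the day before the examination"; the second and third bags follow on the examination day. This arm's intake is introduced with "The oral intestinal preparation process under the guidance of researchers".
- **Arms B and C (hemp seed oil plus 2 L PEG).** "patients orally took 15 mL of hemp seed oil in divided doses at 20:00 and 22:00 1 day before the examination", then two bags of PEG on the examination day. With the first bag, B has 1 L of clear fluids and C has 1000 mL of 5% sugar brine.

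Secondary outcomes include a 0 to 3 tolerance score, "willingness to repeat the same bowel preparation" and adverse events. Objectives makes fewer adverse effects and better tolerance of PEG a stated aim.

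**The concern.** Double-blind tells a reader that neither the participant nor the staff dealing with the participant knows the allocation. The regimens appear to rule that out for the comparisons with standard PEG, because anyone taking or supervising the preparation can see which kind of regimen it is.

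The tolerability objective is at stake. Tolerance, willingness to repeat and symptoms such as nausea, bloating, abdominal pain and dizziness are largely the participant's own report. If the participant knows the regimen, a difference between arms mixes the effect of the preparation with the effect of knowing it. Under a double-blind label a reader would discount the second component, and the Discussion expects the results to influence which regimens are prescribed.

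The endoscopist's assessments depend on a separate matter, namely whether the arm is disclosed to the person scoring.

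**Working it through.** No arithmetic beyond counting applies. The check sets the regimens (Study protocol) against the blinding statement (Recruitment, randomization, and blinding) and then against the outcomes.

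**Step 1. Regimens item by item.**

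| Feature | A | B | C |
|---|---|---|---|
| Hemp seed oil (arm label) | none | 30 mL | 30 mL |
| Intake at 20:00 the evening before | none listed | oil | oil |
| Intake at 22:00 the evening before | PEG plus 1 L clear fluids | oil | oil |
| PEG bags on the examination day | 2 | 2 | 2 |
| PEG bags in total | 3 | 2 | 2 |
| Drink with the first PEG bag | 1 L clear fluids | 1 L clear fluids | 1000 mL 5% sugar brine |

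**Step 2. Which pairs can be told apart.**

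- *A versus B, and A versus C.* The arms differ in product, in number of PEG bags, in whether PEG is taken the evening before, and in the time of first intake (22:00 versus 20:00). A participant who swallows oil and takes two bags is not in A; one who takes three bags and no oil is. A researcher who guides the intake sees the same thing.
- *B versus C.* Oil, clock times, PEG amount and nominal added volume (1 L) are the same. Only the drink differs. The Introduction says the brine was added partly to make PEG taste better, so a taste difference is intended. The article does not say that the drinks look different or that participants could identify their arm.

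So two of the three pairwise comparisons are unmasked by the regimens, and the third is undetermined.

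**Step 3. Could a dummy restore masking?** A double dummy would need a 20:00 intake in A and a third, matching bag in B and C. The timed regimens contain neither. The arm descriptions in the randomization section and the Figure 2 legend name no dummy either. The conclusion therefore rests on what the regimens state, and not only on the absence of the word placebo.

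**Step 4. Which outcomes depend on the participant's knowledge.**

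- *Largely patient-reported:* the tolerance score, willingness to repeat, and most of the adverse events listed under Safety assessments. For A versus B or C these are effectively open-label.
- *Assessed at colonoscopy:* BBPS (primary), cecal intubation time, and polyp and adenoma detection. The endoscopist need not know the regimen, so blinding remains feasible.

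**Step 5. Can the bias be signed or sized?** No. The article reports nothing about what participants expect. Nominal volume does not settle the direction either. By arm label, A has 3 L of PEG and B has 2 L. If the brine is additional to the PEG, C has 2 L + 1 L = 3 L plus oil, the same nominal volume as A before the oil is counted. The text does not make clear whether the accompanying litre in any arm is diluent or extra fluid.

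**The case against.** Four arguments can be made for the plan.

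1. **The blinding sentence is limited to the examination.** Read as the colonoscopy, it covers the endoscopist's assessments. That reading is fair for BBPS, intubation time and detection rates. It does not rescue the statement for participants, who took the preparation hours earlier and still know what they took. Tolerance and symptoms also arise during preparation, before such blinding would begin.
2. **A condensed article may omit the masking procedure, and Figure 2 is not shown.** This is why the fix allows for describing masking actually used. The written regimens nevertheless leave no place for a double dummy. The reference to researchers' guidance is attached to arm A only, so the point about staff is confined to whoever guides intake.
3. **The two-stage unblinding is a real safeguard.** It implies analysis under coded groups. This stands and should be kept, but it protects the analysis and not the participant's report.
4. **Separation of staff roles is operational detail that an article may leave out.** That is accepted; its absence is not held against the plan. It is in the fix because an assessor-blinded description depends on it.

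A reader might also infer more than the documents support: that all three arms are visibly distinguishable and participant blinding is nil throughout (B and C share everything but the drink); that participants expected a smaller volume to be easier, so the bias favours the new regimens (no such expectation is reported, and a smaller total volume in C is not established); that the primary outcome is compromised (it is scored by an endoscopist who can be blinded); or that the registry entry is wrong (the record is not at hand).

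**Conclusion.** The double-blind label and the statement that participants and researchers are blinded do not hold for A versus B or A versus C, given the regimens as written. Tolerance, willingness to repeat and symptom reports are effectively open-label in those two comparisons, which are the ones against the standard regimen. For B versus C, unmasking is possible but not shown. No magnitude or direction of bias can be given.

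The conclusion assumes that the Study protocol section lists each arm's intake in full. If masking not described there was used, the remedy is to describe it. The point does not affect the sample size, the regimens or the feasibility of a blinded primary assessment. It is worth correcting because it changes how firmly the trial can conclude on its tolerability objective.

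**What to change.** Reconcile the Abstract, Trial design and setting, the blinding section and the Discussion with the Study protocol section, in one of two ways:

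- describe the trial as endoscopist (outcome-assessor)-blinded, and keep the analysis under coded groups that the two-stage unblinding implies; or
- if masking was used that the article does not describe, describe it.

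With the first option, also state that:

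- staff who allocate participants or guide intake do not score BBPS;
- participants are asked not to tell the endoscopist which preparation they took;
- tolerance, willingness to repeat and symptom outcomes are reported and interpreted as open-label, at least for A versus B and A versus C.

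No regimen, endpoint or sample size changes. The cost is revised wording in the protocol and the final report, a division of roles among staff, and the loss of the double-blind label.

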### Study protocol

All subjects undergoing colonoscopy should start a no-pigment, low-residue, low-fiber diet 3 days before examination and fast at 18:00 the night before the examination. If hypoglycemia or other discomforts occur due to hunger on the same day, oral colorless vitamin drinks or candy bars can be taken to enhance tolerance. Moreover, to allay the participants’ fear of intestinal preparation, researchers should explain the purpose of colonoscopy, importance of adequate intestinal preparation, and potential adverse events that may occur during intestinal preparation.

Figure 2 depicts the drug use schemes of the 3 groups. The oral intestinal preparation process under the guidance of researchers in the 3 L of PEG group was as follows: one bag of PEG and 1 L of clear fluids was taken orally at 22:00 the day before the examination, the second bag was taken 4–6 h before the examination, and the third bag of PEG was taken half an hour later (Fig. 2A). As for the 30 mL of hemp seed oil and 2 L of the PEG group, patients orally took 15 mL of hemp seed oil in divided doses at 20:00 and 22:00 1 day before the examination, the first bag of PEG and 1 L of clear fluids 4–6 h before the examination, and the second bag of PEG half an hour later (Fig. 2B). Regarding the 30 mL of hemp seed oil, 2 L of PEG, and 5% sugar brine group, patients orally took 15 mL of hemp seed oil in divided doses at 20:00 and 22:00 1 day before the examination, the first bag of PEG and 1000 mL of 5% sugar brine 4–6 h before the examination, and another bag of PEG half an hour later (Fig. 2C). In the study, participants were free to drink clear fluids after the commencement of bowel preparation. The study schedule is shown in Fig. 3.

**Fig. 2 Fig2:**
[figure not shown]
Study protocol for each group. **A** 3 L PEG. **B** 30 mL of hempseed oil and 2 L of PEG. **C** 30 mL of hempseed oil, 2 L of PEG, and 5% sugar brine

**Fig. 3 Fig3:**
[figure not shown]
Study schedule of enrollment, interventions, and assessments. **A** 3 L of PEG. **B** 30 mL of hempseed oil and 2 L of PEG. **C** 30 mL of hempseed oil, 2 L of PEG, and 5% sugar brine. BBPS, Boston Bowel Preparation Scale; ADR, adenoma detection rate; PDR, polyp detection rate

### Study endpoints

#### Primary outcomes

The effect of intestinal preparation was regarded as the main outcome indicator and was scored using the Boston Bowel Preparation Scale (BBPS). As a commonly used clinical bowel preparation assessment scale, the BBPS score divides the large intestine into 3 segments (rectum and sigmoid colon, transverse colon and descending colon, ascending colon and cecum) and scores after adequate bowel preparation. Each intestinal segment was scored from 0 to 3 points, and the total score ranges from 0 to 9 points. The indications of scorings were as follows: 0 points, the entire intestinal mucosa cannot be observed due to irremovable solid or liquid feces; 1 point, parts of the intestinal mucosa cannot be observed due to the presence of stains, turbid liquid, and residual feces; 2 points, the intestinal mucosa is well observed, but a small amount of stains, cloudy liquid, and feces remain; and 3 points, the intestinal mucosa is well observed, and there are no residual stains, cloudy liquids, and stools [39]. In this study, the total score of BBPS score is > 5, and any intestinal segment ≥ 2 points can be considered satisfactory intestinal preparation.

#### Secondary outcomes

Adverse reactions that occur during bowel preparation are the secondary outcome indicators of the study. We evaluated the interval between taking bowel preparation and the first bowel movement, the total number of bowel movements completed, time of cecal intubation, detection rate of polyps and adenomas, willingness to repeat the same bowel preparation, whether the protocol is tolerated (0 points for no discomfort; 1 point for mild discomfort; 2 points for ability to tolerate; 3 points for not being able to tolerate), and adverse events.

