### Sample size

We calculated the expected sample size based on the preliminary extrapolation of the results of bowel preparation before the study began. According to the results of previous studies, when using 3 L PEG for bowel preparation, the qualified rate of bowel preparation was 80%. PEG was accepted as the standard preparation, and the aforementioned percentage was taken as a reference [18, 20, 37, 38]. Assuming the qualified rate of bowel preparation in this study is 85%, the alpha level was set to 0.05. When a sample size of 690 was calculated, a 5% difference between the three groups could be determined.

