### Statistical analysis

In this study, we will adopt intent-to-treat and per-protocol methods to analyze all data. The basic information of patients is expressed by mean, median, and standard deviation. The chi-square test will be used to compare the categorical variables in the basic data of patients. In two independent samples, the Mann–Whitney *U*-test and Student’s test will be used for the comparison of continuous variables; the chi-square test will be used for the comparison of the main results; secondary outcomes will be compared using the chi-square test for categorical variables and Student’s *t*-test for continuous variables. All statistical analyses will be conducted with the 2-tailed test, and *P* < 0.05 will be considered statistically significant. We will make every attempt to collect complete information for all participants and avoid missing data. If necessary, missing data will be handled using multiple imputation. As no formal stopping rules have been specified for this study, no formal interim analyses are planned, and hence, no statistical testing will take place until the final analysis. All data were analyzed using SPSS 26 (SPSS Inc., an IBM Company, Chicago, IL).

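### Cecal intubation time and polyp/adenoma detection are compared by valid tests that leave out the endoscopist, which may cost some precision, mainly for intubation time

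*Protocol article*

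**What the plan says.** The Secondary outcomes section lists, among others, "time of cecal intubation, detection rate of polyps and adenomas". The Statistical analysis section settles how these are compared: "secondary outcomes will be compared using the chi-square test for categorical variables and" Student's t-test for continuous ones. It adds that "All statistical analyses will be conducted with the 2-tailed test".

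Under Recruitment, randomization, and blinding, "the participants were assigned to the following 3 groups in a 1:1:1 ratio"; no stratification by endoscopist is mentioned. The same section says that "researchers, endoscopic physicians, and participants will all be blinded during the examination". That plural is the main indication that several people perform the examinations. Their number and case shares are not given, and the Rescue therapy section speaks of the endoscopist in the singular. Nowhere is the endoscopist named as a stratum, covariate or random effect.

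**The concern.** Time to reach the cecum and the finding of polyps or adenomas depend on the person handling the scope as well as on how clean the bowel is. If operators differ, a two-sample t-test or an unstratified chi-square test leaves that difference in the unexplained variation. The standard error is then larger than it need be, and an effect of the regimen is harder to detect.

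The protocol is not merely silent here, because it names the tests for exactly these outcomes. An analysis that follows it would make no use of the operator even if the code were on file. What is at stake is the precision of some secondary comparisons. The validity of the trial and its primary result are not in question.

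**Working it through.** **Plan's own figure.** The protocol states no power, target difference or standard deviation for these outcomes. The total of 690 was set on the primary outcome, so there is no figure to reproduce for this point. Equal allocation gives 690 / 3 = 230 per arm.

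**Inputs from the protocol.** 230 per arm; two-sided tests; "the alpha level was set to 0.05", so the critical value is 1.96.

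**Inputs assumed.** The share r of the variance of (log) intubation time that lies between endoscopists: 5% to 25%. The power of the unadjusted pairwise comparison: 70%, and 80% as a second case. Operators are spread over the arms by chance.

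**Intubation time.** Adjusting for endoscopist reduces the residual variance by the factor 1 − r, so the standard error falls by sqrt(1 − r). A comparison with 70% power has a standardised effect of 1.96 + 0.524 = 2.484. After adjustment:

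power = Phi(2.484 / sqrt(1 − r) − 1.96), with an equivalent sample size of 1 / (1 − r).

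Example for r = 0.10: 2.484 / 0.949 = 2.619; 2.619 − 1.96 = 0.659; Phi(0.659) = 74.5%. For the 80% case, 2.484 is replaced by 1.96 + 0.842 = 2.802. This corresponds to a difference of 2.802 × sqrt(2/230) = 0.26 SD.

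| Share r between endoscopists | Unadjusted SE relative to adjusted | Power, from 70% | Power, from 80% | Equivalent n per arm, 230 / (1 − r) |
|---|---|---|---|---|
| 0 (or one operator) | 1.000 | 70% | 80% | 230 |
| 5% | 1.026 | 72.2% | 82.0% | 242 |
| 10% | 1.054 | 74.5% | 84.0% | 256 |
| 15% | 1.085 | 76.9% | 86.0% | 271 |
| 20% | 1.118 | 79.3% | 87.9% | 288 |
| 25% | 1.155 | 81.8% | 89.9% | 307 |

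The gain is worth 5% (1/0.95) to 33% (1/0.75) more patients. The formula ignores the few degrees of freedom spent on operators.

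**Polyp and adenoma detection.** A simulation compared the plain chi-square test with a Cochran-Mantel-Haenszel (CMH) test stratified by endoscopist. All its settings are assumptions: 230 per arm, 8 endoscopists, detection of 25% against 37%, and 6,000 trials for each setting. Type I error was simulated at 30% in both arms.

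| SD of operators on the logit scale | Power, chi-square | Power, CMH | Type I error, chi-square | Type I error, CMH |
|---|---|---|---|---|
| 0 | 78.6% | 78.0% | 5.4% | 5.4% |
| 0.3 | 79.8% | 80.0% | 4.7% | 5.0% |
| 0.5 | 79.9% | 80.6% | 5.1% | 5.0% |
| 0.8 | 80.2% | 83.7% | 4.5% | 4.7% |

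Stratifying costs 0.6 point when operators do not differ. It gains 0.2 to 0.7 point under modest variation and 3.5 points under large variation. The type I error of the planned chi-square test stays near 5% throughout.

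**The case against.** The strongest reply is that nothing here is wrong. Unadjusted t-tests and chi-square tests are valid in an individually randomised trial, these are secondary outcomes with no stated power, and adjusting for operator is an optional refinement that an analysis plan could add. The whole size of the gain rests on assumed inputs, and with a single endoscopist it disappears. Validity and dependence on assumptions are both conceded, and they are why the point is minor. What remains is that the protocol itself chose the unadjusted tests for these outcomes, and a more precise comparison costs almost nothing.

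Four stronger readings are tempting, and the protocol does not support them.

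- **Confounding.** A reader might infer that an uneven spread of fast and slow operators would bias the comparison. With individual randomisation and blinded endoscopists, such imbalance is ordinary chance variation, already reflected in the unadjusted standard error.
- **Operator not recorded.** The protocol says "Researchers should collect clinical data, including gender, age, weight, BMI, history of the previous colonoscopy, history of abdominal surgery" and further patient history. That list is open, concerns screening, and also omits intubation time and lesion findings, which must be collected. It shows nothing about whether the operator is recorded. The Data management section says the case report form holds all data needed, and the form is not shown.
- **Operator as the dominant source of variation.** The protocol gives no figure for this, and the range assumed above leaves 75% to 95% of the variance elsewhere.
- **Bowel-preparation scores as the operator's own reading.** The Primary outcomes section does not say who scores the Boston scale, so the point does not extend to the primary outcome.

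**Conclusion.** The point holds as a minor matter of efficiency. The planned tests are valid but leave out the endoscopist, although more than one is implied, so any variation between operators stays in the error term. For intubation time, an assumed variance share of 5% to 25% between endoscopists means that a comparison with 70% power would have about 72% to 82% after adjustment. For polyp and adenoma detection the expected gain is about 0 to 1 point, unless operators differ greatly. With one operator there is no gain. The number of endoscopists, their case shares and the variance share are all unknown from the protocol, so the actual loss cannot be computed.

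**What to change.** Make sure the endoscopist's code is recorded for each examination. In the Statistical analysis section, state that cecal intubation time will be compared on the log scale in a linear model with treatment arm and endoscopist as factors, and fix before unblinding how low-volume endoscopists are pooled. For polyp and adenoma detection, a Mantel-Haenszel comparison stratified by endoscopist may replace the plain chi-square test, with little gain expected.

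The cost is one data field, if it is not already held, a sentence or two in the analysis section, a few degrees of freedom and the pooling rule. Effects on intubation time would then be reported as ratios. If one person performs all examinations, no change is needed and the protocol could simply say so.
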